**Fig. 1 Fig1:**
[figure not shown]
Study Flow Chart

Primary endpoint: Pathological complete response rate (pCR%) based on Ryan’s 0–3 pathological tumor regression grade (TRG) system [20].

Secondary endpoints: R0 resection rate, three-year disease-free survival (3-y DFS), five-year overall survival (5-y OS) and safety.

The study started in October 2019. Local ethics committee approvals are expected in October 2020, the enrollment of the first patient in November 2020, the last patient completing the research in November 2027, database lock in June 2027 and publication in June 2028.

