### Grouping

All eligible patients will be registered, pre-enrolled and receive three cycles of SOX. After tumor response evaluation using RECIST 1.1, patients achieving CR or PR will be enrolled [19]. Then randomization without stratification will be carried out by computer generated allocation using IBM SPSS Statistics 22, and enrolled patients will be randomly assigned (1:1) to Arm A or Arm B.

Arm A: Patients will be pre-enrolled and receive three cycles of SOX. After randomization, patients in Arm A will receive three more cycles of SOX (six cycles of neoadjuvant chemotherapy with SOX in total) followed by D2 gastrectomy. After which postoperative chemotherapy will not be recommended.

Arm B: Patients will be pre-enrolled and receive three cycles of SOX. After randomization, patients in Arm B will receive D2 gastrectomy (three cycles of neoadjuvant chemotherapy with SOX in total). After which postoperative chemotherapy using SOX will be recommended.

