### Sample size calculation

The primary endpoint of this trial is pCR rate. Based on the data from previous study, after three cycles of SOX, the PCR rate is about 7% (*p*_*0*_), and we estimated that with six cycles of SOX, the PCR rate can be increased to 15% (*p*). Based on the Z test, the null and alternative hypotheses are *H*_*0*_: *p*=*p*_*0*_; *H*_*1*_: *p*≠*p*_*0*_. With the statistical power of 0.8 (β=0.2), the type I error rate of 0.05 (α=0.05), when *Z* > marginal value, the *H*_*0*_ will be rejected and *H*_*1*_ will be accepted. Using the following formulas with the sampling ratio is 1:1 and the drop-out rate of 10%, the sample size is set at 262 per arm [23].
$$ n=p\left(1-p\right){\left(\frac{z_{1-\frac{\alpha }{2}}+{z}_{1-\beta }}{p-{p}_0}\right)}^2 $$Each participant center takes 400 to 1000 cases of gastric cancer per year and about 2% of patients can be enrolled. Thus recruitment can be completed in 2 years.

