### Statistical analysis

The pCR rate is defined as the rate of patients achieving pCR. The R0 resection rate is defined as the rate of R0 resection. The DFS is defined as the period from the time of surgery to recurrence or death. The OS is defined as the period from the time of surgery to death or last follow-up. Chi-square test will be used to compare patients’ characteristics, pCR rate and R0 resection rate between two arms. Survival curves will be estimated by the Kaplan-Meier method. Survival rate of DFS and OS will be compared respectively between two arms using a two-sided log-rank test. Both intention-to-treatment analysis (ITT, patients who receive any treatment after enrollment) and per-protocol analysis (PP, patients who receive all preoperative chemotherapy and surgery) will be performed. Missing data will be processed using multiple imputation. For loss of follow-up, ITT analysis and sensitivity analysis will be performed respectively.

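### The blanket multiple-imputation rule does not exempt pCR, so unresected patients could be given an imputed response, which favours the arm with more loss before surgery

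*Protocol article*

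**What the plan says.** The primary endpoint, listed under Methods with Figure 1, is "Pathological complete response rate (pCR%) based on Ryan’s 0–3 pathological tumor regression grade (TRG) system". The Statistical analysis section adds that "The pCR rate is defined as the rate of patients achieving pCR", compares the arms by chi-square test, and gives one rule for incomplete data: "Missing data will be processed using multiple imputation". A separate sentence deals with loss to follow-up through ITT and sensitivity analyses.

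Two analysis sets are named: "intention-to-treatment analysis (ITT, patients who receive any treatment after enrollment") and "per-protocol analysis (PP, patients who receive all preoperative chemotherapy and surgery"). Enrollment comes after the first three cycles (Grouping: "After tumor response evaluation using RECIST 1.1, patients achieving CR or PR will be enrolled"). After randomization "patients in Arm A will receive three more cycles of SOX" before surgery, whereas Arm B goes to gastrectomy. The Sample size calculation section allows for "the drop-out rate of 10"%, not split by arm or by reason.

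**The concern.** A regression grade can be read only from a resected specimen. A randomised patient who is not resected because of progression, toxicity, refusal or death has no grade, but also has not achieved pCR. The outcome is known to be a failure, and nothing about it is missing at random. The article does not say this, and its only explicit rule for absent values is imputation.

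The analysis sets decide who is affected. An Arm A patient who starts cycle 4 has received treatment after enrollment and stays in the ITT set even if never resected, so that patient's pCR could be imputed. In Arm B the first treatment after enrollment is the operation, so a patient who never reaches it appears to drop out of the ITT set. Imputing in one arm and excluding in the other lead to the same place: each arm's rate approximates the rate among resected patients. The contrast then ignores pre-surgical loss and favours the arm with more of it. Arm A has three further three-week cycles (3 × 3 = 9 weeks) in which such loss can occur. The per-protocol analysis is no check on this, because it excludes unresected patients by definition.

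**Working it through.** **Inputs from the article.** pCR 7% after three cycles and 15% after six; two-sided α 0.05; power 0.80; 1:1 allocation; 10% drop-out; 262 per arm (Sample size calculation).

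**Assumptions.** The unresected fractions by arm (10%/10%, 15%/5% and 20%/5%, A/B) are assumed, because the article gives none. The imputation model is assumed to contain arm alone.

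**1. The plan's own figure.** Two-sample formula with pooled variance: n = [1.96·√(2·0.11·0.89) + 0.842·√(0.07·0.93 + 0.15·0.85)]² / 0.08² = 239. Allowing for drop-out gives 239/0.9 = 266 or 239 × 1.1 = 263. The unpooled version gives 237, then 264 or 261. The stated 262 is within four patients of all of these, so 15% vs 7% at 262 per arm is a fair base.

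**2. Effect on the estimate.** Let r be the pCR rate among resected patients and d the unresected fraction. Counting unresected patients as non-pCR gives r(1 − d). Imputing on arm alone gives (1 − d)r + d·r = r. Excluding unresected patients also gives r. With r = 15% (A) and 7% (B):

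| Unresected A/B | A, as randomised | B, as randomised | Difference | Reported | Overstated by |
|---|---|---|---|---|---|
| 10%/10% | 0.15 × 0.90 = 13.5% | 0.07 × 0.90 = 6.3% | 7.2 | 8.0 | 8.0/7.2: 11% |
| 15%/5% | 0.15 × 0.85 = 12.75% | 0.07 × 0.95 = 6.65% | 6.1 | 8.0 | 8.0/6.1: 31% |
| 20%/5% | 0.15 × 0.80 = 12.0% | 6.65% | 5.35 | 8.0 | 8.0/5.35: 50% |

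**3. Effect on the type I error.** Suppose the true rate among all randomised patients is 10% in both arms.

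- 15%/5%: the resected rates are 0.10/0.85 = 11.76% and 0.10/0.95 = 10.53%, a difference of 1.24 points, on 262 × 0.85 = 223 and 262 × 0.95 = 249 patients. SE = √(0.1176·0.8824/223 + 0.1053·0.8947/249) = 0.029, so the shift is 0.43 SE. Rejection = Φ(−1.96 + 0.43) + Φ(−1.96 − 0.43) = 7.1%.
- 20%/5%: the rates are 12.5% and 10.53%, and the same steps give 10.1%.

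A simulation (262 per arm, within-arm imputation, 20 imputations, 4,000 runs) gave rejection rates of 5.3% at 10%/10%, 7.3% at 15%/5% and 9.9% at 20%/5%. Scoring unresected patients as non-pCR gave 5.3%, 5.7% and 5.4%.

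**4. Power when unresected patients count as non-pCR.** Pooled z, 262 per arm, two-sided 5%:

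- 13.5% vs 6.3%: 79%
- 12.75% vs 6.65%: 66%
- 12.0% vs 6.65%: 56%

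**The case against.** The strongest reply is that the article never says an unresected patient's pCR is missing. On the ordinary meaning of a rate of patients achieving pCR, such a patient has not achieved it, so there is nothing to impute. That reading is open and may be the intended one. A reader might infer that the plan will impute pCR for unresected patients; the text does not establish that. What stands is that the article does not exclude imputation, so two analysts could reach different primary results from the same data.

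Secondly, imputation variables and models usually belong in the SAP or the full protocol, and neither is shown. That is so, and the absence of a model is not the point here. The point is the stated rule, which has no limit and, if applied to the primary endpoint, is unsuitable.

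Thirdly, multiple imputation need not reproduce the resected rate. The Tumor response and toxicity criteria section schedules a RECIST evaluation after cycle six, and a model using it could assign a low pCR probability to a patient who progressed. The figures above therefore describe the arm-only model and not the method in general.

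Fourthly, the only documented loss is 10% overall, and the Discussion expects responder selection to reduce early termination for poor efficacy. A reader might infer that the type I error is inflated in any case. It is not: at 10%/10% there is no inflation. Greater loss in Arm A is plausible from the longer preoperative course, but the article does not document it.

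**Conclusion.** The point holds as a defect in a stated rule for the primary analysis. Imputation is unrestricted, no text scores unresected patients as non-pCR, and the ITT definition appears to keep such patients in Arm A while losing them in Arm B. If the rule is applied to pCR, both arms approximate resected-only rates.

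The size depends on the assumed loss by arm and on imputation by arm alone. At balanced 10% loss it is modest: 0.8 points, with the error rate intact. It becomes material only if loss clearly differs between arms: 1.9 points and about 7% error at 15%/5%, and about 10% error at 20%/5%. The article supports neither a claim that bias is certain nor any particular loss split.

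**What to change.** Make three changes together in the analysis text:

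- Define the primary analysis set as all randomised patients, analysed as allocated. This replaces the present ITT definition and should be presented as a change.
- Count every patient in that set without a resection specimen as non-pCR, and as non-R0 for the R0 rate.
- Limit multiple imputation to resected patients whose pathology is unavailable and to covariates. Report the resected-only rate as a sensitivity analysis.

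The first two belong together. Scoring non-resection as failure within the present ITT set could penalise Arm A alone: at 10%/10% loss, if every unresected Arm A patient had started cycle 4, the contrast would be 13.5% vs 7.0%, or 6.5 points instead of 7.2.

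The cost is a few sentences of text, slightly lower pCR rates in both arms, and some power. At 262 per arm, power is about 79% with 10% loss in each arm, but about 66% at 15%/5% and 56% at 20%/5%. The 79% should not be quoted as if it held whatever the loss.

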### Management and quality control

Each participating surgical team performs over 200 gastrectomies with D2 lymphadenectomies. Each researcher has over 20 years of professional experience. The role of clinical research organization (CRO) is filled by Beijing Sinocro PharmaScience Co.,Ltd. The lead center and CRO will organize periodical training in standard operating procedure (SOP) of gastroscopy, enhanced CT, EUS, MRI, pathological examination, staging and response evaluation. Local PI will be responsible for staging, observation of D2 completion and identification of eligible patients. To address interrater disparities, three researchers will perform the evaluation. The central review for observation and evaluation will be conduct.

CRO will appoint and authorize clinical research associates (CRA) as monitors throughout the trial according to the SOP. CRA are responsible for regularly monitoring case report forms (CRF), ensuring compliance with the protocol and GCP regulations, and checking completeness, consistency and accuracy of data. Researchers will work with CRA to ensure that any problems can be solved. Through the Electronic Data Capture System (EDC), the lead center will have the right to obtain all data and report the results. Other participating centers will only have the right to obtain the data from their own centers.

The test drugs will be purchased by the patients at their own expense according to medical orders, and the pharmacies of participating centers will be responsible for distributing them. The patients will take the medicine and make records in the patient diaries, which will be regularly monitored by CRA.

National Medical Products Administration of China and Human Genetic Resource Administration of China will inspect the trial and fulfillment of legal requirements.

## Discussion

The RESONANCE-II study was conducted to evaluate the efficacy and safety of different cycles of SOX as neoadjuvant chemotherapy for patients with locally advanced gastric cancer. The primary endpoint of the study is the rate of pathological complete response. A study evaluated the histopathological tumor regression in 480 gastric cancer patients who received surgery after neoadjuvant chemotherapy. The results showed that complete or subtotal tumor regression was an independent prognostic factor for survival, which suggested that pathological complete regression could be regarded as a proper endpoint for neoadjuvant trials in gastric cancer [24]. Moreover, our study aims to evaluate the efficacy of preoperative chemotherapy. Using pCR rate as the primary endpoint instead of survival could reduce the influence of surgery and postoperative chemotherapy on the endpoint. Also, less time will be required to get the primary results. Therefore, we chose pCR rate as the primary endpoint. However, to illustrate the relation between tumor regression and survival thoroughly, further research is still needed.

In our study, eligible patients will be pre-enrolled and receive 3 cycles of SOX. Those who achieve CR or PR will be enrolled and considered as subjects with cancer that is sensitive to SOX chemotherapy. As for patients achieve SD or PD, they will be considered as subjects with tumors that are not sensitive to SOX chemotherapy and will be excluded. The purpose of this setting is to answer the question of whether more cycles of preoperative chemotherapy should be applied when it is effective in short-term application. When preoperative chemotherapy shows little effectiveness, other treatments will be recommended instead of continuing to apply chemotherapy. In addition, pre-enrollment can ensure the completion of chemotherapy after randomization and reduce the early termination of chemotherapy due to poor efficacy. Therefore, in our opinion, the design is appropriate.

The total number of cycles of preoperative and postoperative chemotherapy in most trials is about six to eight [8–10]. In this study, patients in group A who receive 6 cycles of neoadjuvant chemotherapy can be considered to have completed all perioperative chemotherapy. It will be recommended that these patients could not receive adjuvant chemotherapy with close monitoring after surgery if there is no evidence of disease progression. Relevant results of group A may suggest the feasibility of applying only preoperative chemotherapy in gastric cancer.

To avoid bias, uniform inclusion and exclusion criteria will be applied and randomization will be performed. To prevent loss to follow-up, investigators will keep timely and effective contact with patients and provide a user-friendly mobile phone application for patients to contact investigators and record medications. All radiologists, endoscopists and pathologists will not participate in any process relevant to grouping or intervention and they will not have access to any chemotherapy-related or surgery-related records. SOPs will be defined and used with sufficient training. The CRO will monitor throughout the project.

To the best of our knowledge, this study is the first phase III randomized trial to compare the cycles of neoadjuvant chemotherapy using SOX for resectable locally advanced cancer. Due to the relatively high efficacy and safety of SOX neoadjuvant chemotherapy, it can be widely used for treatment of resectable locally advanced gastric cancer. We hope that the results of this trial can provide theoretical basis for setting an optimal duration of neoadjuvant chemotherapy.

## Data Availability

The data and materials of the study will be made available on request.

## Abbreviations

SOX: S-1 combined with oxaliplatin
WHO ICTRP: World health Organization international clinical trails registry platform
XELOX: Capecitabine and oxaliplatin
ECF: Epirubicin, cisplatin and fluorouracil
CF: Fluorouracil plus cisplatin
FLOT: Fluorouracil plus leucovorin, oxaliplatin and docetaxel
ECF/ECX: Epirubicin, cisplatin and fluorouracil or capecitabine
SC: S-1 plus cisplatin
PC: paclitaxel plus cisplatin
RECIST: Response evaluation criteria for solid tumors
SD: Stable disease
PD: Progressive disease
CR: Complete response
PR: Partial response
pCR%: The rate of pathological complete response
3-y DFS: Three-year disease free survival
5-y OS: Five-year overall survival
ECOG: Eastern cooperative oncology group
AJCC: American joint committee on cancer
CT: Computer tomography
EUS: Endoscopic ultrasonography
MRI: Magnetic resonance imaging
Hb: Hemoglobin
PLT: Platelet count
ALT: Alanine aminotransferase
AST: Aspartate aminotransferase
SCr: Serum creatinine
ALB: Serum albumin
ULN: Upper limit of normal
Ccr: Creatinine clearance rate
ECG: Electrocardiogram
DPD: Dihydropyrimidine dehydrogenase deficiency
BID: Bis in die (twice a day)
BSA: Body surface area
NYHA: New York heart association
NCI-CTC AE: National cancer institute common toxicity criteria for adverse event
GCP: Good clinical practice
ITT: Intention-to-treat
PP: Per-protocol
NCCN: National comprehensive cancer network
CSCO: Chinese society of clinical oncology
TRG: Tumor regression grade
CRO: Clinical research organization
SOP: Standard operating procedure
CRA: Clinical research associate
CRF: Case report form
EDC: Electronic data capture
